The analysis and the discussion of the pilot study results took place at an international workshop held in October 2001 in Dresden. Based on the results and experience gained during the pilot study, conclusions were drawn and changes in the study design were made.

The baseline examination was performed 4 to 8 weeks after the insertion of the prosthetic restorations by external investigators chosen randomly among the investigators of the other participating dental schools. The examinations had to be pooled to reduce the traveling costs. Approximately 10% of the patients were examined twice on a random basis by both the local and the external investigator. This applied also to all follow-up examinations.

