### Randomization - implementation

The data of any potentially eligible patient, who contacted one of the participating study centers, were documented during the screening process. Once a patient had given his/her informed consent, the data forms with clinical findings and treatment planning were sent to the treatment coordinator (TC). The TC checked the data regarding their conformity with the study protocol and sent a randomization request to the biometrical center. Finally, the TC forwarded the randomization results to the dental clinics.

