### Statistical methods

All statistical analyses are intended to be performed on the basis of the intention-to-treat principle, i.e. according to the patient's randomized treatment allocation regardless of any later protocol violations. In order to assure that treatment groups are balanced and provide structural equality, baseline patient characteristics will be compared between groups. For the primary outcome measure, Kaplan-Meier survival analyses will be performed. The Mantel-Cox log-rank test will be applied to test the null hypothesis of the equal progression of tooth loss in both treatment groups. This particular hypothesis test constitutes the primary study result and provides confirmatory statistical evidence. In order to quantify to what extent the risk to lose teeth differs between the treatment groups, the hazard ratio will be estimated on the basis of a univariate proportional hazards model. Beyond the primary analysis, analyses of prespecified secondary outcome measures will be performed. In further exploratory analyses, possible prognostic factors of tooth loss will be identified applying the multivariate Cox regression as well as classification and regression tree (CART) analyses.

Descriptive analyses generally comprise the calculation of location and scale statistics (mean and standard deviation) as well as rates of target events. Point estimates will be supplemented by 95% confidence intervals. Inductive statistical analyses will be performed using appropriate significance tests. In order to compare both treatment groups with respect to quantitative measures, the Mann-Whitney U test will be applied, and Fisher's exact test will be used for the qualitative factors. The statistical analyses will be performed by means of the software packages SPSS (Version 17 for Windows, SPSS Inc., Chicago, USA) and SAS (Version 9.2 for Windows, SAS Institute Inc., Cary, NC, USA).

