### Enrollment, assessment, and follow-up

The enrollment for the pilot study was stopped at 36 patients, with 19 patients randomized for therapy A and 17 randomized for therapy B. Three patients dropped out after the randomization; in one of these cases, the treatment had been performed already. Two hundred and fifteen patients were enrolled in the main trial, with 109 patients randomized for treatment A and 106 for treatment B (Fig. 4). The follow-up appointments were scheduled at 4 to 8 weeks (baseline) and at 6, 12, 24, 36, 48, and 60 months after finishing the treatment (Table 3).

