**Figure 4 F4:**
[figure not shown]
**Number of patients randomized and patients treated compared to the number originally scheduled**.

**Table 3 T3:** Examinations

Examination Type	Examination time	Investigator
**Screening**	Every patient complying with the inclusion criteria regardless of his/her participation in the trial	Any dentist involved

**Pretreatment examination**	Before randomization, after giving informed consent	The dentist performing the treatment

**Insertion**	During insertion	Local investigator

**Recall after insertion**	1, 3 and 14 days after insertion	Local investigator

**Baseline**	4-8 weeks after insertion	Local investigator/external investigator (randomized selection)

**Recall**	6 months, 12 months, 2, 3, 4, 5 years after insertion	Local investigator/external investigator (randomized selection)

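### The rank test named for quantitative secondary outcomes uses neither the pre-randomization findings nor the stratification factors, so it gives up some precision

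*Protocol article*

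**What the plan says.** The Statistical methods section fixes a Kaplan-Meier and log-rank analysis for tooth loss and then turns to the other outcomes: "Beyond the primary analysis, analyses of prespecified secondary outcome measures will be performed". Fisher's exact test is named for qualitative factors. For quantitative ones the text reads: "In order to compare both treatment groups with respect to quantitative measures, the Mann-Whitney U test will be applied". No covariate, clinic term, age term or repeated-measures model is attached to these comparisons. Multivariable Cox regression and CART appear only as exploratory tools for prognostic factors of tooth loss. On estimation, the section adds: "Point estimates will be supplemented by 95% confidence intervals".

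Three other parts of the article bear on this.

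- Table 3 lists a pretreatment examination, timed "Before randomization, after giving informed consent". The section on implementing the randomization says that forms holding clinical findings and the treatment plan went to the treatment coordinator before allocation was requested.
- The section on sequence generation describes permuted blocks within each clinic and two age groups, split at 50 years.
- The section on enrollment and follow-up sets seven post-treatment appointments: "The follow-up appointments were scheduled at 4 to 8 weeks (baseline) and at 6, 12, 24, 36, 48, and 60 months after finishing the treatment". The visit labelled baseline is therefore a post-treatment visit. The Outcomes section confirms it: "The baseline examination was performed 4 to 8 weeks after the insertion of the prosthetic restorations by external investigators".

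**The concern.** The secondary outcomes carry the trial's stated interest in periodontal health, function and quality of life. The discussion reports that fewer patients were recruited than expected, so information per patient matters. A two-sample rank test with no covariates leaves between-patient variation in the error term, although part of it could be explained by values recorded before allocation. It also ignores the factors used to stratify randomization, while the discussion itself counts the dentists and the treatment environment among the most important confounders.

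At stake is the width of the intervals and the power for secondary comparisons. Type I error is not at stake.

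**Working it through.** **The plan's own figure.** The only sample size stated is 70 per group, and it belongs to tooth loss. With 5% switching in each direction the rates become 0.95 × 20% + 0.05 × 5% = 19.25% and 0.95 × 5% + 0.05 × 20% = 5.75%. The hazard ratio is ln(0.9425)/ln(0.8075) = 0.277. Schoenfeld's formula at 75% power and two-sided 5% gives 17 events. With 10% exponential dropout over 5 years that is 71.5, or 72 per group, close to the stated 70. This does not bear on the quantitative secondary outcomes, for which the article gives no SD, effect size or power.

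**Inputs.** From the article: 109 and 106 patients randomized, and 10% loss by 5 years. Assumed: the correlation r between pre-randomization and follow-up values (none is given), and normality for the comparison with the rank test, where Mann-Whitney has efficiency 0.955 relative to the t test.

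**Formulas.**

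- Adjusted variance of the treatment difference relative to unadjusted: 1 − r².
- Equivalent unadjusted sample size: 215/(1 − r²).
- Standard error in SD units: √(1/109 + 1/106)/√0.9 = 0.1364/0.9487 = 0.1438.
- Effect detectable with 80% power, two-sided 5%: (1.960 + 0.842) × 0.1438 = 0.403 SD for a t test. For Mann-Whitney it is 0.403/√0.955 = 0.412 SD. For ANCOVA it is 0.403 × √(1 − r²).

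| Assumed r | Variance factor | Reduction | 215 patients count as | Detectable effect (SD) | Power at 0.4 SD |
|---|---|---|---|---|---|
| Mann-Whitney, unadjusted | – | – | – | 0.41 | 78% |
| 0.2 | 0.96 | 4% | 224 | 0.39 | 81% |
| 0.3 | 0.91 | 9% | 236 | 0.38 | 83% |
| 0.5 | 0.75 | 25% | 287 | 0.35 | 90% |
| 0.7 | 0.51 | 49% | 422 | 0.29 | 97% |

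The fourth column compares adjusted with unadjusted means. The last two columns compare ANCOVA with Mann-Whitney, so they also include the 4.5% normal-theory loss from ranking. That loss can vanish or reverse for skewed data.

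**Would change scores do the same job?** Under equal variances, change from the pre-randomization value has relative variance 2(1 − r): 1.6, 1.4, 1.0 and 0.6 at r = 0.2, 0.3, 0.5 and 0.7. Each exceeds the matching 1 − r². Below r = 0.5 the change score is worse than no adjustment.

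**Where r may be low.** In the main trial, randomization was moved ahead of completed pretreatment (Discussion). The Intervention section then requires pretreatment to bring periodontal measures within set limits, which alters the values recorded earlier. Table 3 also has the treating dentist make the pre-randomization examination, and local or external investigators the later ones. Both points argue for the lower rows for periodontal measures.

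**Stratification factors.** The article gives no between-clinic or between-age-group variance, so this part of the gain cannot be sized.

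**The case against.** The strongest reply is that the article offers one generic sentence and leaves the rest to documents not shown. It does not name the visit, say whether raw values or changes are tested, or describe how missing visits are handled. That stands, and it rules out several stronger readings. A reader might infer that the plan tests visit by visit, drops patients who miss a visit, or contradicts itself by pairing a rank p-value with a mean difference. None of this is stated. Means and standard deviations are listed as descriptive statistics, and no mean difference is promised for secondary outcomes.

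A reader might also assume that every secondary outcome has a pre-randomization value. The article does not show this. The forms are said to hold clinical findings; OHIP is not mentioned there. Measures such as the marginal fit of a new restoration cannot have such a value.

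Nor is the rank test itself a fault. Many outcomes in Table 1 are graded indices, for which ranks are defensible and a linear mixed model is not clearly better.

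What the reply does not remove is that the named test is a stated choice, not an omitted detail. It takes no covariate or stratum. Running it on change scores is not excluded, but would use the earlier value less efficiently than adjustment does.

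**Conclusion.** The point holds as a matter of precision. The named test is valid under randomization, and the confirmatory log-rank analysis is untouched. For outcomes that were recorded before randomization, ignoring that value forgoes a variance reduction of 4% to 49% over assumed correlations of 0.2 to 0.7. The low end is plausible for periodontal measures. In detectable effect, that is 0.41 SD with Mann-Whitney against 0.39 to 0.29 SD with adjustment, under normality and 10% loss. Where no earlier value exists, only the unsized gain from clinic and age group remains. This is a worthwhile and cheap improvement to secondary analyses, and not a flaw in the trial's main conclusion.

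**What to change.** For each quantitative secondary outcome recorded before randomization, compare the arms at 5 years with adjustment for that value, age group and clinic. Use the pre-randomization value and not the 4 to 8 week visit labelled baseline: that visit follows treatment, and adjusting for it could remove part of the effect.

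- Approximately continuous outcomes: ANCOVA, or a mixed model over the scheduled visits with the 5-year contrast. Report the adjusted mean difference with its 95% confidence interval.
- Ordinal or skewed scores: rank ANCOVA, or a stratified (van Elteren) rank test. Fourteen clinics by two age groups is 28 strata, about 215/28 = 7.7 patients each, so strata will be small.
- No pre-randomization value: adjust for the stratification factors only.
- Keep the unadjusted Mann-Whitney test as a sensitivity analysis.

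The outcomes in each class should be listed before the data are analyzed. The article describes the trial as ongoing, so this is feasible. No new data are needed. The cost is extra programming and some model assumptions for secondary outcomes.

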### Enrollment, assessment, and follow-up

The enrollment for the pilot study was stopped at 36 patients, with 19 patients randomized for therapy A and 17 randomized for therapy B. Three patients dropped out after the randomization; in one of these cases, the treatment had been performed already. Two hundred and fifteen patients were enrolled in the main trial, with 109 patients randomized for treatment A and 106 for treatment B (Fig. 4). The follow-up appointments were scheduled at 4 to 8 weeks (baseline) and at 6, 12, 24, 36, 48, and 60 months after finishing the treatment (Table 3).

**Figure 4 F4:**
[figure not shown]
**Number of patients randomized and patients treated compared to the number originally scheduled**.

**Table 3 T3:** Examinations

Examination Type	Examination time	Investigator
**Screening**	Every patient complying with the inclusion criteria regardless of his/her participation in the trial	Any dentist involved

**Pretreatment examination**	Before randomization, after giving informed consent	The dentist performing the treatment

**Insertion**	During insertion	Local investigator

**Recall after insertion**	1, 3 and 14 days after insertion	Local investigator

**Baseline**	4-8 weeks after insertion	Local investigator/external investigator (randomized selection)

**Recall**	6 months, 12 months, 2, 3, 4, 5 years after insertion	Local investigator/external investigator (randomized selection)

## Discussion

Traditionally, the treatment decisions in dentistry were based on empirical knowledge and in-vitro investigations of dental materials. During the last decade, clinical trials were carried out more frequently. However, high-level evidence is lacking regarding many treatment-related questions in dentistry due to:

(1) controversial opinions concerning feasible outcome measures in clinical studies (subjective, objective),

(2) long observation periods, particularly for the research in restorative dentistry,

(3) high treatment expenses and laboratory costs, and

(4) difficulties with regard to randomization and blinding respectively.

The aim of the majority of studies in restorative dentistry was to prove whether or not a treatment can be considered effective. The outcome measures used in dentistry usually focused on technical failures (restoration still present, survival rates) so far. Some studies considered biological aspects, for example periodontal condition and need of endodontic treatment. In recent years, the evaluation of patient-related factors and the oral health related quality of life have been gaining importance. While the majority of the previous studies had a retrospective design and relatively limited variable sets, this trial is aiming at a more comprehensive evaluation of the prosthetic treatment. This approach required the collection of a large-scale variable set. However, some of the very specific examinations used in the pilot study proved to be less meaningful than expected. Furthermore, it was difficult to train some of the respective diagnostic measures (Table 1). A multitude of the collected data resulted from the comprehensive evaluation of the prosthetic treatment methods and restoration types. This multitude of data could compromise the practicability. Considering the basic aim of the trial, it was vital to focus on those clinical findings that might lead to an explanation for the success or failure of a treatment concept, the onset of TMD, and patient satisfaction.

Discussions at the international symposium held after the recruitment phase of the pilot study revealed the treatment workflow as further cause for the limited number of patients recruited. The pilot study protocol demanded a completed pretreatment (i.e. caries, periodontitis) before randomization. The pretreatment sometimes required the removal of existing restorations without being able to give the patient a clear treatment perspective. Therefore, the treatment workflow was changed to randomization at an earlier stage.

Clinical trials on the long-term outcomes of prosthetic treatments are extremely costly and time-consuming. The observation periods required are long. The complexity of the prosthetic treatment measures and the common allocation practice with regard to the differential indication of fixed versus removable restorations [28] turn the randomized trial design into the only option feasible.

The most important confounders in prosthetic treatment studies are the dentists themselves, the applied treatment principles, and the treatment environment. The multi-center approach involving almost half of the German dental schools and the extensive training of the dentists are considered appropriate to reduce this bias and appear to be suitable to deliver results that are representative for the basic conditions of German dental-schools.

The main inclusion criteria define a certain topography where all molars are missing in one jaw and at least both canines and one premolar are present on each side (Fig. 1). This is an appropriate condition to study the differential indication between removable (treatment A) and fixed (treatment B) restorations and an ideal field to gather comparable data on the clinical performance of these fundamentally differing treatment concepts. However, the number of cases was lower than expected because of problems during the patient recruitment phase and an overestimation of the number of eligible subjects (Fig. 4). Due to methodological reasons, the inclusion criteria had to be chosen in a manner that the two fundamentally differing treatment concepts could be applied with similar chances of success and therefore be comparable accordingly. This applies to the suitable dental status as well as to the exclusion of conditions that might compromise one of the treatment concepts, for example malocclusion in treatment B. Even the multi-site approach, numerous advertisements in local newspapers, and further measures to support the recruitment proved to be insufficient to raise the number of patients targeted.

Following the holistic approach, clinical findings were applied that are commonly used in the daily practice. Only few diagnostic measures applied in clinical dentistry have been validated (e.g. periodontal probing depth) including the possibility to gather clinical data in a reproducible way and, thus, allow the calibration of the clinical investigators. In general, surrogate parameters as caries and attachment loss have widely been used in prosthetic treatment studies. They are suitable to deliver relatively early results and were, therefore, included as secondary outcome measures. However, tooth loss as the irreversible sequel of the main dental diseases has a high reliability and a high impact on health and was, therefore, chosen as a very viable indicator of oral health.

The study can be considered as one of the most comprehensive randomized trials in prosthetic dentistry. The design with its basic principles established the basis for clinical research in restorative dentistry on a contemporary level. Considering the basic aim of the trial, it was vital to focus on those clinical findings that might offer an explanation for the success or failure of a treatment concept, the occurrence of TMD, and, not least important, patient satisfaction.

## List of abbreviations used

ASA: American Society of Anesthesiologists; CART: Classification and Regression Trees; CDA: California Dental Association; DFG: Deutsche Forschungsgemeinschaft (German Research Foundation); EN: Europäische Norm (European Standard); ISO: International Organization for Standardization; OHIP: Oral Health Impact Profile; RaSDA: The Randomized Shortened Dental Arch Study; RDP: Removable Dental Prosthesis; RDPs: Removable Dental Prostheses; SDA: Shortened Dental Arch; SOP: Standardized Operating Procedure; TC: Treatment Coordinator; TMD: Temporomandibular Disorders.
